10.8.2 Objectives

Our specific aims are:

To collect health dairies recording the incidence and duration of common infectious illnesses in approximately 800 subjects enrolled in our clinical trial of vitamin D and calcium.

To assess the effects of vitamin D supplementation on the risk of upper respiratory tract infections and explore effects on gastrointestinal illnesses, using formal standardized case definitions of URTI, ILI, and AGI

Our primary hypotheses are:

Supplementation with vitamin D3 (1000 IU/day) reduces the number of winter episodes of URTI.

Supplementation with vitamin D3 (1000 IU/day) reduces the number of winter days affected by URTI.

Our exploratory hypotheses are:

Supplementation with vitamin D3 (1000 IU/day) reduces the number of episodes of URTI over a year of observation.

Supplementation with vitamin D3 (1000 IU/day) reduces both the number of winter episodes of ILI and the number of winter days affected by that illness.

Supplementation with vitamin D3 (1000 IU/day) reduces both the number of episodes of AGI and the days affected by that illness.

In addition, we will (i) compare the recent reporting of colds and ILI by subjects telephoned every 6 months among those randomized to vitamin D3 (1000 IU/day) supplementation or placebo; and (ii) examine the impact of serum levels of 25-hydroxyvitamin D3 (25-OHD) on subject’s experience of symptoms during the study.

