10.8.4 Analyses

URTI: We define a common cold or upper respiratory tract infection (URTI) as the presence of 2 or more of the following: runny nose, nasal congestion, sneezing, sore throat, cough, swollen or tender neck glands.

ILI: We define Influenza-like illness (ILI) as fever, plus 2 or more of the following: sore throat, cough, muscle ache, headache.

AGI: We will base our definition of acute gastrointestinal illness on Payment’s “highly credible gastrointestinal illness”: either 1) vomiting or watery diarrhea; or 2) nausea or soft diarrhea with abdominal cramps.

Further, our definition of an episode of illness requires 6 symptom-free days before a subsequent episode will be said to have occurred. We will require this symptom-free interval because we assume that symptoms occurring toward the end of an illness may not necessarily fulfill the case definition but will still be part of the episode. For example, on days 1, 2 and 3, a participant’s symptoms fulfill the definition of a common cold (sore throat and nasal congestion). On days 4 and 5 only a mild sore throat persisted, but the nasal congestion recurred on days 6 and 7, which together with the sore throat fulfill the case definition for those two days. According to our definitions, this constitutes only one episode of URTI. For the purposes of estimating “days of illness”, we will use our case definitions strictly, so that day 4 and 5 are excluded, and there were only 5 days of URTI altogether.

Statistical methods

Primary end points will be the number of episodes of each type of illness and the total number of days of affected by the illness. Because of the seasonally low vitamin D levels in winter, our main hypothesis is that supplementation will have an effect during those months, rather than during the summer.

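### Colds and Flu study: Section 10.8.2 names two primary measures and Section 10.8.4 names six, so influenza-like and gastrointestinal illness are exploratory in one place and primary in the other

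*Protocol*

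**What the plan says.** Section 10.8.2 (Objectives) has two separate lists.

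- **Primary:** vitamin D3 "reduces the number of winter episodes of URTI", and vitamin D3 "reduces the number of winter days affected by URTI".
- **Exploratory:** URTI episodes over a full year; for ILI, that vitamin D3 "reduces both the number of winter episodes of ILI and the number of winter days affected by that illness"; for AGI, that it "reduces both the number of episodes of AGI and the days affected by that illness".

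The specific aims in the same section match these lists. They speak of assessing effects on upper respiratory infection but only of exploring effects on gastrointestinal illness.

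Section 10.8.4 (Analyses) gives case definitions for URTI, ILI and AGI, and then, under statistical methods, says: "Primary end points will be the number of episodes of each type of illness and the total number of days" affected by the illness. The sentence after it cites low vitamin D levels in winter and says "our main hypothesis is that supplementation will have an effect during those months, rather than during the summer".

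Section 10.8.5 (Sample size) gives placebo rates and describes power in words for winter URTI episodes and winter URTI days. It says nothing about ILI or AGI.

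**The concern.** A protocol should give one answer to the question of which results decide the study. Here ILI and AGI carry the exploratory label in one section and the primary label in another. Both are current text, and nothing else in Section 10.8 says which governs.

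The difference matters when the results are mixed. Suppose winter URTI episodes and days show no effect and one of the four ILI or AGI measures has p < 0.05. Under 10.8.2 the study is negative with an exploratory signal. Under 10.8.4 a primary end point has been met. The choice between the two readings could then be made after the data are seen.

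This is not a detail deferred to an analysis plan. The protocol has fixed the primary set twice, in two ways, and any analysis plan written from it must depart from one of the sections.

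**Working it through.** **Step 1. Set the sections side by side.**

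| Measure | Section 10.8.2 | Section 10.8.4, end-point sentence | Section 10.8.5, power reasoning |
|---|---|---|---|
| URTI episodes, winter | primary | primary | yes |
| URTI days, winter | primary | primary | yes |
| ILI episodes | exploratory (winter) | primary | none |
| ILI days | exploratory (winter) | primary | none |
| AGI episodes | exploratory | primary | none |
| AGI days | exploratory | primary | none |

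The count is 1 illness × 2 measures = 2 in 10.8.2, and 3 illnesses × 2 measures = 6 in 10.8.4. Four measures change status. The end-point sentence names no season. The sentence after it supplies winter for the main hypothesis, which goes some way to settling season and leaves illness type open. Full-year URTI episodes, exploratory in 10.8.2, are therefore best read as outside the six.

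**Step 2. Look for a stated error rate.** There is none to reproduce. Section 10.8 gives no significance level, test order or multiplicity rule. The two-sided 0.05 in Section 13.5 is for the parent trial. The statements in Sections 10.5.5 and 10.7.4 that multiple testing will not be adjusted for belong to the mammography and participant-beliefs studies. The next step therefore assumes 0.05 two-sided per test with no adjustment.

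**Step 3. Chance of at least one false positive among k true null hypotheses.**

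For independent tests this is 1 − 0.95^k:

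- k = 2: 1 − 0.9025 = 9.75%
- k = 4 (ILI and AGI alone): 1 − 0.8145 = 18.5%
- k = 6: 1 − 0.7351 = 26.5%

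For correlated tests, the statistics were simulated as z_i = √ρ·c + √(1−ρ)·e_i, with c and e_i standard normal (400,000 draws). The proportion of draws with any |z_i| > 1.96 was:

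| ρ | 2 end points | 4 end points | 6 end points |
|---|---|---|---|
| 0.3 | 9.5% | 17.4% | 24.1% |
| 0.5 | 9.0% | 15.5% | 20.8% |
| 0.8 | 7.8% | 11.4% | 13.8% |

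Going from two to six end points adds 26.5 − 9.75 ≈ 17 percentage points at ρ = 0 and 13.8 − 7.8 = 6 points at ρ = 0.8.

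**Step 4. Count only false positives in the direction of benefit** (z_i > 1.96, nominal 2.5%). Six end points give 14.0% at ρ = 0 and 6.9% at ρ = 0.8. Two give 5.0% and 3.9%.

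**The case against.** The best defence is that one loosely drafted sentence stands against two sections that agree. Section 10.8.2 labels ILI and AGI exploratory in so many words, and 10.8.5 gives sample-size reasoning for winter URTI alone. The sentence in 10.8.4 follows three case definitions and could be read as naming the two kinds of measure taken for each illness. The season is supplied one sentence later. This is good evidence of what was intended, and it shows which section should yield. It does not remove the contradiction, because the sentence calls these measures primary for every illness and nothing in 10.8 withdraws that.

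A reader might go further and infer that all six end points are to be tested at full alpha. The document does not say so. The 0.05 level is borrowed from the parent trial, and sharing error between end points is commonly left to an analysis plan, which is not at hand. That stronger reading should not be made.

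The objection to the size also has force. Equal correlation across six measures is a simplification: episodes and days of one illness are linked by construction, and the URTI and ILI definitions share sore throat and cough. Two-sided rates also count false signals of harm. For these reasons the result is given as a range, with the benefit-direction figures beside it. The rates for two end points are only the comparator; having two primaries is not itself the fault.

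**Conclusion.** The contradiction holds and does not depend on any calculation: two primary measures in 10.8.2, six in 10.8.4, with the four ILI and AGI measures changing status. The winter sentence addresses season and leaves illness type unresolved.

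The numerical consequence is conditional. At an assumed two-sided 0.05 per test, unadjusted and with equal correlation between 0.8 and 0, the chance of at least one false positive is about 14% to 27% for six end points and about 8% to 10% for two. In the benefit direction only, it is about 7% to 14% against about 4% to 5%.

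The scope is limited. This is an ancillary diary study in approximately 800 subjects. A reader should not infer any effect on the parent trial's adenoma end point or its error rate; nothing in Section 10.8 bears on either. The text should be corrected, but the point does not threaten the main trial.

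**What to change.** Replace the end-point sentence in Section 10.8.4 with one that follows Section 10.8.2, for example: *The primary end points are winter URTI episodes and winter URTI days; full-year URTI, ILI and AGI measures are exploratory.*

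How the two primaries share the error rate is for the sponsor to decide and state. No ordering is prescribed here. In particular, making days conditional on episodes would not follow from 10.8.2, which puts the two on an equal footing. It would also gate the measure that 10.8.5 describes as better powered at a relative risk of 0.8: power there is called excellent for days and adequate for episodes.

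The change is to one sentence and alters no data collection. Its cost is that an ILI or AGI result can no longer be claimed as primary.

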10.8.5 Sample size

Based on national data and data from our own study, we estimate that placebo subjects experience between 0.6 and 0.9 URTI winter UTRI per year on average. With our expected recruitment, we will have excellent statistical power to detect vitamin D relative risks of 0.7 or lower, and adequate statistical power for relative risks of 0.8. Based on national data, we estimate that placebo subjects experience between 1 and 3 days affected by a winter URTI per year on average. With our expected recruitment, we will have excellent statistical power to detect vitamin D relative risks of 0.8 or lower.

10.8.6 Additional Risks

This sub-study presents no additional physical risk to the subjects. Serum 25-OHD was already collected for the parent study. Confidentiality of data is the primary concern, but the data are not sensitive and are well protected as described earlier.

10.8.7 Benefits and importance of knowledge to be gained

There is no direct benefit to subjects. We aim to describe whether vitamin D prevents colds and flu; the answer to this question will benefit society as a whole.

10.8.8 Inclusion of women, minorities

The sub-study was available to subjects of all demographic categories within the parent study.

***11.0 Safety Monitoring and Reporting Adverse Events***

*11.1 Definition, Monitoring and Follow-up*

An adverse event is any condition that appears or worsens after the subject is enrolled in an investigational study. Adverse events may be discovered as a result of study lab measurements or during regular study interviews (every six months). As a safety measure, blood levels of calcium, creatinine and 25-OH vitamin D will be monitored one year, and where applicable three years after randomization. At each regularly scheduled interval contact (every six months) study coordinators will monitor symptoms, medical diagnoses and hospitalization as part of the subject case report form. Adverse events may also be discovered by subject-initiated contact at any time. All adverse events that meet study specific criteria are documented on an Adverse Event Report Form. There are three types of events that have been defined: Perceived Toxicity, Diagnosis and Out-Of-Range Lab Result. All adverse events, including laboratory abnormalities that in the opinion of the Clinical Director are clinically significant, will be followed up according to good medical practice, and documented as such*.*

*11.2 Adverse Event Information and Severity*

The following information will be collected on the Adverse Event Report Form: start and stop dates, severity (grade), relationship to study agents, and whether or not the subject stopped taking the study agents due to the adverse event. Severity will be graded by a numerical score according to the NCI Common Terminology Criteria for Adverse Events (CTCAE - version 3.0 or newer). Events not included in the defined NCI CTCAE will be scored according to their impact on the subject’s abilities to perform daily activities as follows:

a. Mild (causing no limitation of usual activities)

b. Moderate (causing some limitation of usual activities)

c. Severe (causing inability to carry out usual activities)

*11.3 Serious Adverse Events*

Serious adverse events are defined as those events that meet any of the following criteria:

- Results in death
- Is immediately life threatening
- Requires inpatient hospitalization or prolongation of existing hospitalization
- Results in persistent or significant disability or incapacity
- Is a congenital anomaly or birth defect

*11.4 Reporting*

Adverse events will be reported to study center IRBs according to local IRB policy. Study Centers are responsible for reporting all adverse events to the Project Coordination Center according to the requirements and timelines set forth in the standard operating procedures for this study. Unexpected serious adverse events possibly related or related to the study agents will be reported on an expedited basis to the NIH, the FDA (as required by law), Pfizer Pharmaceuticals, previously Wyeth Consumer Healthcare, and the Safety and Data Monitoring Committee. In addition, every six months the Safety and Data Monitoring Committee will monitor study-wide adverse events and the overall conduct of the trial. Subsequently, a report summarizing study-wide adverse events will be sent to each Study Center for submission to the individual IRBs.

***12.0 Data Management***

*12.1 Central database*

The central database was developed using a SQL-based database management application and will be administered by the Informatics group within the Section of Biostatistics and Epidemiology at Geisel School of Medicine at Dartmouth. Any data errors or inconsistencies detected after data entry will be automatically tracked, communicated and resolved using the Informatics center's web-based application. An audit trail of all data changes over the life of the study will be maintained. The database is located on a server protected by firewalls using stateful inspection firewalling and protocol and application inspection. Access to the database server will no be allowed by users on computers outside of the firewall protected zone.

*12.2 Website*

This study will employ real-time web-based data entry at the Study Centers. A central study website will provide ready and secure access to entry interfaces and current study information including contact information for all study personnel, the study protocol, policies and procedures, updated forms and questionnaire versions, and real-time reports. The web server will run Apache on Linux OS and Microsoft IIS Server on Windows NT, providing a high level of security through authentication and 128 bit encryption using SSL. The website was developed using HTML, Java, Javascript, and PDF-formatted documents, and will be accessible from all current browsers. A separate study web page will be used to provide access to subjects for self-completion of interval questionnaires.

*12.3 Data Entry*

Most data entry will occur when the study coordinator is able to interview subjects in a location with a networked computer so that data can be entered in real time into forms or questionnaires served from the Dartmouth web server. The study coordinator will access the database interface through the study URL, be authenticated, link to the appropriate form, and enter data directly into the central database. Data will be checked in real time via scripted validation for range, data type, field length, and logical consistency with related data fields. These routines will prompt the coordinator to reconcile inappropriate or inconsistent data, and will not permit missing mandatory data. Critical data (such as study identification number) will be double-keyed. Additionally, to reduce entry error, appropriate data will be pulled from related tables within the central database and will be used to create pull-down menus and pick-lists for data entry whenever possible. Study coordinators will be encouraged to use this electronic (validated) data entry whenever possible. Subjects will also be able to enter data directly into interval questionnaires on the web.

If internet access is temporarily disabled or unavailable, a low-tech backup (paper forms) will be provided to ensure timely data collection under any circumstance. All data that is collected on paper forms will subsequently be entered into the electronic study forms on the web by the study coordinator. Electronic data entry must occur within 7 days of data collection. Double entry will be required.

Electronic study questionnaires, which are administered to subjects by their study coordinator, will include the intake questionnaire (to be used at the intake appointment), the first phone interview questionnaire (to be used during the initial phone interview at randomization assessment), the interval questionnaire (to be used during interviews mainly by phone), every six months throughout the study, the end of treatment questionnaire, and the observational follow up questionnaire. Paper versions of these questionnaires are provided for completion by subjects as necessary (post randomization only), and for IRB review.

*12.4 Computer Security and Safety*

All computer systems and programs will be password protected, and all electronic communications of study and other confidential information will be encrypted. Good computer security practice (restricting physical access to machines, prohibition of password sharing, logging off computers after work hours or when away from the machine) will be required of all study personnel. Virus protection software will be installed on each study machine. The virus detection tools will be used, maintained, audited and, if necessary, updated on all computers and pathways into the system. All computer systems will be updated regularly with any applicable operating system and application security patches. System access to computer systems will be audited. Redundant backups and off-site backup storage will allow for quick restoration of data in the unlikely event that a hardware failure, disaster, or security breach should occur. Servers and backups will be located in a secured location with access limited to authorized personnel.

*12.5 Archiving*

All study raw data, forms, documents, software programs, software applications and computer data files will be indexed and archived routinely. Strict version control of documents and software applications will be instituted. Retention of study documentation after study completion will conform to FDA and NIH requirements.

*12.6 Reports*

Standardized study management reports will be generated monthly during the recruitment phase of the study and thereafter at least every quarter for the Project Coordinator at the Dartmouth Project Coordination Center. These reports will be used to track study progress including subject enrollment, randomization, compliance, subject status changes, and study events. The data will be reported for each Study Center individually and summarized for the study as a whole.

Every six months, a standardized report will also be generated for the Safety and Data Monitoring Committee meeting. This report will include additional information on clinical events and adverse events that is coded by blinded treatment group. Other than the study statistician and statistical analyst, no study personnel will see this report.

***13.0 Statistical Methods***

### 13.1 Hypotheses

Our main hypotheses are:

1. Supplementation with vitamin D3 (1000 IU/day) reduces the risk of new adenomas in patients with a recent history of these tumors.

2. Supplementation with calcium carbonate (1200 mg elemental calcium/day) reduces the risk of new adenomas

3. Supplementation with both vitamin D3 (1000 IU/day) and calcium carbonate (1200 mg elemental calcium/day) reduces the risk of new adenomas more than supplementation with calcium carbonate alone.

Our secondary hypotheses are:

4. Supplementation with vitamin D3, or with vitamin D3 or with calcium carbonate, reduces the risk of new advanced colorectal lesions (colorectal cancer and adenomas with an estimated diameter of one centimeter or greater, those with tubulovillous or villous histology, or those with advanced dysplasia).

5. Supplementation with vitamin D3 will have a greater effect among individuals whose initial serum 25-OH vitamin D level is less than the overall study median, compared with subjects whose levels are greater than the median.

6. The effect of supplementation with vitamin D3 will be modified by polymorphisms at the 3' end of the vitamin D receptor gene.

### 13.2 Sample Size Justification

The sample size for this trial will be approximately 3000 enrolled subjects. Based on our previous trials, we expect that at least 80% of subjects will complete the run-in period, leaving 2400 patients randomized. Of these, we expect that 60% will be male and 40% female. Assuming that 35% of females agree to be randomized to calcium, we expect to have 1776 subjects randomized in the full factorial design and an additional 624 women (taking calcium) randomized to vitamin D or placebo. In our previous trials, we obtained follow-up examinations from at least 95% of subjects; however, we will assume conservatively that the follow-up rate will be 92%. This translates to endpoint data for 408 subjects randomized to each of the four supplement combinations in the factorial design (1632 in total) and for an additional 287 females randomized to each of the two vitamin D groups (574 in total). For the primary comparison of vitamin D versus no vitamin D, we expect 1103 subjects (408 + 408 + 287) per group with follow-up data. For the primary comparison of calcium versus no calcium, we expect 816 subjects (408 + 408) per group with follow-up data. For the primary comparison of vitamin D + calcium versus calcium alone, we expect 695 subjects (408 +287) per group with follow-up data.

Data from our latest trial -- the Aspirin/Folate Polyp Prevention Study -- indicate a three year adenoma occurrence rate of 45% among placebo subjects (who were asked to avoid NSAID use). NSAID use by the study subjects may lower the expected adenoma occurrence rate in the proposed study. Assuming that aspirin confers a 20% decrease in occurrence risk and 33% of subjects take aspirin daily, we would expect the overall occurrence rate in placebo subjects to be 42%. However, we expect that the subjects who enroll in this study will have lower risk profile overall because fewer high-risk subjects will be recruited. Thus, for the purpose of power computations, we assume that the occurrence rate among placebo subjects will be 37%. Power calculations are based on standard formulae for power of the 2 test and assume no interaction between the supplements. Power for the vitamin D effect assumes a calcium relative risk of rc = 0.80, and power for the calcium effect assumes a vitamin D relative risk of rd = 0.75. Table 1 (below) shows the statistical power to detect various differences in occurrence risk for the primary comparisons of adenoma occurrence rates. The results indicate that we will have good statistical power to detect relative risks of 0.80 or less for the marginal vitamin D effect and the marginal calcium effect. We will have adequate power to detect a relative risk of 0.75 or less for the effect of vitamin D in the presence of calcium.

The detectable relative risk for the vitamin-D-by-calcium interaction effect is approximately rcd = 0.60 (or 1.67). This was determined based on a z-test comparing log relative risks assuming adenoma occurrence rates as follows: placebo alone, p; calcium alone, rcp, vitamin D alone rdp, and vitamin D + calcium, rcdrdrcp, where rc = 0.80, rd = 0.75 and p = 0.37.

| Table 1. Statistical power* for primary study comparisons | | | | | | |
| --- | --- | --- | --- | --- | --- | --- |
|  | |  | Relative Risk | | | |
| Comparison (expected control occurrence) | N per group | | 0.70 | 0.75 | 0.80 | 0.85 |
| Vitamin D vs. no vitamin D (32%) | 1103 | | > 0.99 | 0.99 | 0.92 | 0.70 |
| Calcium vs. no calcium (32%) | 816 | | > 0.99 | 0.95 | 0.82 | 0.57 |
| Vitamin D + calcium vs. calcium (30%) | 695 | | 0.97 | 0.88 | 0.70 | 0.46 |
| *Statistical power is based on a chi-squared test with a 2-sided alpha level of 0.05. Calculations assume a baseline occurrence rate of 37% among placebo subjects and no interaction between the supplements. Power for vitamin D comparisons assumes a relative risk of 0.8 for calcium, and power for calcium comparisons assumes a relative risk of 0.75 for vitamin D. | | | | | | |

We will also have good statistical power to detect interaction effects between vitamin D supplementation and VDR genotype. The total expected sample size of 2206 patients with follow-up data will be used in these analyses, since all patients will be randomized in the vitamin D component of the study, and all patients will be assessed for VDR genotype. The statistical power calculations, given in the table below (Table 2) as the interaction relative risks detectable with 80% power, assume that VDR genotype is classified as two groups (positive and negative), the prevalence of the variants ranges from 20% to 50%, and the marginal relative risk for vitamin D supplementation is 0.75. The calculations also assume that the adenoma occurrence rate in the control group is 32% and VDR-genotype has no marginal effect on recurrence rates. For interaction effects between vitamin D levels (above versus below the median) and vitamin D supplementation, the same computations apply, using the 50% prevalence.

| **Table 2. Detectable relative risks for the interaction effect of vitamin D supplementation and VDR genotype.** | | | | |
| --- | --- | --- | --- | --- |
|  | Prevalence of VDR genotype | | | |
|  | 20% | 30% | 40% | 50% |
| Detectable RR | 0.59 | 0.64 | 0.66 | 0.67 |

